| 24-hour after surgery | Salivary amylase  HADS STAI  Visual analog scale for postoperative pain  QOR  Rescue analgesics usage |

※The allowable range is ± 12 hours before and 24 hours after surgery.

⑤ Sample size

In this study, we plan to perform Bayesian analysis. In this method, the posterior probability of the response rate is calculated by an interim analysis, and the calculated posterior probability is monitored. If it is judged that the effect is not as good as that of untreated, the test should be discontinued. Is planned. In addition, since the posterior predictive distribution is obtained based on the data obtained from the interim analysis, it is possible to judge whether the additional data follows the distribution, and it is possible to save the number of cases by performing this procedure. Is known to be. As an interim analysis, an exploratory analysis will be performed when 20 cases in a group are reached based on reference [1]. Recalculate the required number of cases based on the results of the interim analysis. Regarding the design of the number of cases, referring to the previous study, 1-β was 80%, the significance level was 0.05, and the success rate of the intervention group (yokukansan was expected to be taken preoperatively and preoperatively: impression at the outpatient clinic of pain clinic) is set to 75%. About 40 cases are expected in each group. The clinically meaningful difference is defined as σ = 0.3.

[1]Young-Chang Arai, et al, Evidence based Complementaly and Alternative Medicine.2014; ID965045

⑥ Study endpoints

Primary endpoint: Salivary amylase level

Secondary endpoint: HADS STAI QOR Pain VAS

⑦ Analysis method

Statistical analysis methods are planned to be performed by the maximum likelihood estimation method and the Bayesian statistical method. All analysis is performed by a person in charge of analysis different from that of the principal investigator.

For maximum likelihood estimation methods, t-tests that do not correspond to continuous variables, Fisher's exact test for scale classification, and Mann-Whitney U test for continuous variables or ordinal variables that do not follow a normal distribution such as VAS. A test will be used to determine P <0.05 as significant.

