For Bayesian statistics, the difference between two independent groups is estimated for the primary endpoint. A pre-analysis will be conducted based on the uniform distribution obtained in the exploratory test and the data of 20 subjects, and the obtained distribution will be used as the prior distribution to generate and verify the posterior distribution using the data of 40 subjects in each group.

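### As worded, the final Bayesian analysis of the primary endpoint appears to count the interim patients twice, which makes the posterior too narrow

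*Protocol*

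**What the plan says.** Two parts of section 4 of the protocol bear on this.

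- **Item ⑤, Sample size.** As the interim analysis of this trial, "an exploratory analysis will be performed when 20 cases in a group are reached". For the whole trial, "About 40 cases are expected in each group". The required number is to be recalculated after the interim.
- **Item ⑦, Analysis method.** In the Bayesian part, "the difference between two independent groups is estimated for the primary endpoint". The first step is described as follows: "A pre-analysis will be conducted based on the uniform distribution obtained in the exploratory test and the data of 20 subjects". The second step takes what comes out of the first, and that "distribution will be used as the prior distribution to generate and verify the posterior distribution using the data of 40 subjects in each group".

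Item ⑦ also plans frequentist tests with a 0.05 significance threshold. It does not say which of the two approaches is decisive.

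**The concern.** Using an interim posterior as the next prior is sound only if the likelihood that follows contains none of the data already in that prior. Here the second step uses 40 per group, which is the full size expected in item ⑤. The 20 subjects of the first step match the number at which the interim is triggered, and both items call that look exploratory. Read together, the interim patients supply the prior and are then part of the 40.

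If so, the posterior claims more information than the trial has collected. It would be too concentrated, its centre would lean towards the patients enrolled first, and the evidence on salivary amylase would look firmer than it is. This is not a detail left to a separate analysis plan: the protocol itself names the prior and the data, and the pair as named does not fit together.

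**Working it through.** **Inputs**
- Final size: about 40 per group (section 4 ⑤).
- Interim: 20 cases in a group (section 4 ⑤); 20 subjects, without saying per group, in section 4 ⑦.
- Final prior and data: as quoted from section 4 ⑦.
- Assumptions made here: normal model with a common known SD, flat starting prior, exactly 40 per group at the end, no early stopping.

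**1. Is 40 per group the whole trial?** The plan gives "1-β was 80%, the significance level was 0.05", an intervention success rate of 75%, and "The clinically meaningful difference is defined as σ = 0.3". Reading 0.3 as a difference in rates implies 45% in controls, which is an assumption. With mean rate 0.60, the two-sided formula without continuity correction gives

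n = [1.960 × √(2 × 0.60 × 0.40) + 0.842 × √(0.75 × 0.25 + 0.45 × 0.55)]² / 0.30² = 40.7, so 41 per group.

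Power at 40 per group is 79.3%. The stated figure is thus reproduced as a complete sample size, not as the number still to be enrolled after an interim.

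**2. Each patient used once.** The posterior variance of the difference is 2 SD²/40. The 95% half-width is 1.96 × √(2/40) = 0.438 SD and coverage is 95%. A flat prior updated with all 40 per group gives this result. So does the interim posterior from that flat prior (20 per group) updated with the 20 new patients per group, since 20 + 20 = 40.

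**3. As worded, 20 per group reused.**
- Nominal information: 20 + 40 = 60 per group. Half-width 1.96 × √(2/60) = 0.358 SD.
- Width relative to the correct one: √(40/60) = 0.816, so 18% too narrow.
- With S1 and S2 the sums of the first and second 20 in a group, the group estimate is (2·S1 + S2)/60. The first 20 carry 40/60 = two thirds of the weight instead of half.
- True variance per group, in units of SD²: (4 × 20 + 20)/60² = 0.0278. Nominal: 1/60 = 0.0167. SD ratio: √(0.0278/0.0167) = 1.291.
- Coverage of a nominal 95% interval: 2Φ(1.96/1.291) − 1 = 87.1%. Zero is excluded in 12.9% of null trials.
- A simulation of 400,000 trials gave 87.2% coverage, and 95.0% when each patient was used once.

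**4. As worded, 20 in total reused (10 per group).**
- Nominal information: 10 + 40 = 50 per group. Relative width √(40/50) = 0.894, so 11% too narrow.
- True variance: (4 × 10 + 30)/50² = 0.0280. Nominal: 1/50 = 0.0200. SD ratio 1.183.
- Coverage: 2Φ(1.96/1.183) − 1 = 90.2%. Zero is excluded in 9.8% of null trials.

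**5. Dependence on the final size.** With m per group reused and n per group at the end, true over nominal variance is (n + 3m)/(n + m). This falls towards 1 as n grows, so a larger recalculated sample size reduces the error. It does not vanish while the final data include interim patients.

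**The case against.** The strongest reply is that the overlap is inferred. Section 4 ⑦ does not say in so many words that the interim patients re-enter the likelihood. The sentence is a translation and could mean ordinary sequential updating that finishes once 40 per group have been observed. Section 4 ⑤ lends this some support, because it treats data arriving after the interim as distinct. That remark, however, is about checking new data against a predictive distribution, not about which data form the final likelihood. If sequential updating was meant, the sentence does not say so, and an analyst who follows it literally would count patients twice. The other two escapes have no footing. Forty new patients per group would make 60 in all, which is planned nowhere. An outside pilot is not described either, since the cited study is given as the basis for the timing of the interim, not as a source of patients. What stands is that the overlap should be stated as the apparent meaning, not as a certainty.

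Three stronger readings are tempting and are not supported:
- **That the reused patients are certainly 20 per group.** Section 4 ⑦ says only 20 subjects; the per-group reading comes from section 4 ⑤. It is the likelier one, but both must be carried.
- **That the chance of a false claim more than doubles.** With 20 in total the factor is 9.8/5 = 1.96, just under two.
- **That 10–13% is the trial's false-positive rate.** The protocol gives no credible interval, posterior threshold or rule for a Bayesian claim. Its only stated significance criterion belongs to the frequentist tests, and the double counting arises only in the Bayesian updating.

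**Conclusion.** The point holds as a fault of wording with a real numerical consequence. Taken as written, the prior and the likelihood of the final Bayesian analysis share patients, and the posterior for the primary endpoint is too narrow under either reading of the 20: by 18% (coverage about 87%) or by 11% (coverage about 90%). These figures rest on a normal model with known SD, 40 per group at the end and no early stopping; the direction does not depend on them. The two-sided error of about 10–13% illustrates the miscalibration under a rule that the protocol does not state. The fault is confined to the Bayesian analysis of the primary endpoint.

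**What to change.** Reword the Bayesian paragraph of section 4 ⑦ so that each patient enters the likelihood exactly once. Either of these will do:

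- update the starting uniform prior once, with all patients in the final data set; or
- take the interim posterior from that same uniform prior and update it only with patients enrolled after the interim.

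Under the same model the two give the same posterior, but only if the starting prior is the same in both. The new sentence should also say whether the 20 are per group or in total, and should refer to the patients in the final data set instead of a fixed 40, since the number may be recalculated.

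The change is one sentence. It needs no extra patients or measurements. The price is a wider, correctly calibrated posterior: in the example above, a half-width of 0.438 SD instead of 0.358 SD.

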**5. [Policies for selecting research subjects]**

(1) Research subjects

① Patients aged 20 to 60 years who have been diagnosed with breast cancer and undergo total mastectomy and sentinel lymph node biopsy, or partial mastectomy and sentinel lymph node biopsy at Niigata University Medical and Dental Hospital or Niigata Prefectural Cancer Center Niigata Hospital

② Patients who received written and oral explanations regarding this study and showed their consent to participate in writing.

(2) Exclusion criteria

① Patients with preoperative condition classification (ASA-PS) 4 or higher by the American Society of Anesthesia

② Patients with BMI (Body Mass Index ≥ 30)

③ Patients who already have pain that requires oral painkillers somewhere in the body except for the primary disease

④ Those who are allergic to the drug used

⑤ Persons with hypokalemia

⑥ Patients taking anti-anxiety drugs and antipsychotic drugs

⑦ Patients who are already taking painkillers including opioids

⑧ Patients who have already taken some Chinese medicine

⑨ Patients who have difficulty communicating (dementia, mental retardation, mental illness, do not understand Japanese, etc.)

⑩ Other patients who are judged to be inappropriate by the principal investigator and the investigator

(3) Cancellation criteria

① When the research subject offers to decline participation in the research or withdraws consent

② When the entire research is canceled

③ When the result of intraoperative sentinel lymph node biopsy is positive and axillary lymph node dissection is performed

④ When the person in charge of research determines that it is appropriate to discontinue the research for other reasons.

(4) Voluntary research cooperation and freedom of withdrawal

Participation in the study is decided by the patient's free will, and it is possible to withdraw participation at any time. If the patient withdraws from the study before the start of oral administration, it will be excluded from this study. Patients who refuse to take the second dose after the first dose and withdraw from the study are also excluded from this study. Explain that withdrawal of research participation does not result in any disadvantage in subsequent treatment.

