**4. [Research method and period]**

① Research implementation period

From November 1, 2017 to March 31, 2021.

② Information on drugs used

Name: Tsumura Yokukansan (Product number: 054)

Route of administration, dosage and administration: Oral, 1 packet (2.5 g) at a time

Dosage form: Extract granules

③ Research subjects

Patients aged 20 to 60 years who undergo breast cancer surgery at Niigata University Medical and Dental Hospital or Niigata Prefectural Cancer Center Niigata Hospital and undergo total mastectomy and sentinel lymph node biopsy, or partial mastectomy and sentinel lymph node biopsy (Details will be described later).

④ Research method

Multicenter / Open Label / Superiority test by forced random sampling

[1] A pre-treatment questionnaire survey will be conducted on all subjects, and the age, BMI, surgical history, and general status (American Society of Anesthesiologists-Physical Status: ASA-PS, ECOG-PS) will be recorded in advance. Also, before taking the study drug, record the measurement of amylase in saliva, the Hospital anxiety and depression scale (HADS), and the State Trait Anxiety Inventory (STAI).

[2] Subjects are assigned to two groups, one with yokukansan (intervention) and the other without (control), according to the results of randomization. The intervention group should be given 1 packet (2.5 g) of TSUMURA Yokukansan before sleep on the day before surgery and 1 packet (2.5 g) 2 hours before entering the operating room on the day of surgery. For the purpose of maintaining the same quality between the two groups, a forced allocation algorithm is created, and if a bias is confirmed between the groups, forced allocation is performed based on age, surgical history, etc.

[3] Subjects in the intervention group take 1 packet of yokukansan orally 2 hours before entering the operating room on the day of surgery, and then all participants are measured salivary amylase in the operating room. Anesthetized by general anesthesia in the operating room and undergo total or partial mastectomy and sentinel lymph node biopsy

[4] Record salivary amylase measurements, HADS, STAI, visual analog scale of pain: VAS, QOR (Quality of recovery), and the presence or absence of analgesic use 24 hours after surgery.

| 24-hour before surgery | Salivary amylase  HADS STAI |
| --- | --- |
| Just before surgery | Salivary amylase |

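### Total and partial mastectomy at two hospitals are pooled without naming operation or hospital as a balancing factor or stratum, which costs a little precision on pain VAS and QOR

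*Protocol*

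**What the plan says.** - **Who is enrolled** (Protocol, section 5 (1), repeated in section 4 ③): patients who "undergo total mastectomy and sentinel lymph node biopsy, or partial mastectomy and sentinel lymph node biopsy". Either of two named hospitals may enrol them. This gives two operations and two sites in one comparison.
- **How the arms are balanced** (section 4 ④ [2]): "if a bias is confirmed between the groups, forced allocation is performed based on age, surgical history, etc". Operation and hospital are not named.
- **What is recorded beforehand** (section 4 ④ [1]): "the age, BMI, surgical history, and general status (American Society of Anesthesiologists-Physical Status: ASA-PS, ECOG-PS) will be recorded in advance", together with salivary amylase, HADS and STAI. Planned operation and hospital are not on this list.
- **How the outcomes are tested** (section 4 ⑦): an unpaired t-test, Fisher's exact test, and the "Mann-Whitney U test for continuous variables or ordinal variables that do not follow a normal distribution such as VAS". No stratum or covariate is mentioned. In the Bayesian part, "the difference between two independent groups is estimated for the primary endpoint", so it does not reach VAS or QOR.
- **Where pain sits** (section 4 ⑥): "Secondary endpoint: HADS STAI QOR Pain VAS". The primary endpoint is salivary amylase. VAS and QOR are listed only at the assessment 24 hours after surgery.

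**The concern.** The two operations differ in extent, and anaesthesia is described only as general, so the text does not show whether practice is the same at both hospitals. Either factor could plausibly affect pain and recovery at 24 hours. Both are known before a patient is allocated, so they could be balanced and used in the analysis at almost no cost. VAS and QOR have no baseline value of their own to adjust for, which makes other pre-allocation predictors more useful than usual.

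Pain is in the trial's title, and section 3 says that no clinical study has yet examined this drug for postoperative pain. With about 40 patients per arm, the pain comparison should not carry variation that could easily be removed. At stake are some power and the readability of the result if one arm happens to contain more total mastectomies than the other.

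**Working it through.** **The plan's own figure.** Section 4 ⑤ gives a 75% success rate under intervention, 80% power, a significance level of 0.05 and a meaningful difference of 0.3. That difference is written as σ and is read here as a difference in proportions, so control = 45%. With mean proportion 0.60 and two-sided testing:

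n = [1.96·√(2·0.60·0.40) + 0.8416·√(0.75·0.25 + 0.45·0.55)]² / 0.3² = (1.358 + 0.555)² / 0.09 ≈ 40.7, so 41 per group.

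This agrees with the stated figure of about 40, which is not in dispute. It concerns a success rate. The protocol gives no power for VAS.

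**Inputs for the pain comparison.** From the protocol: 40 per arm. Assumed, because the documents do not give them: half the patients have each operation; within-operation SD of the 24-hour VAS is 20 mm; total mastectomy changes mean VAS by D = 5, 10 or 15 mm.

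**Step 1: how often the arms differ in operation mix.** The difference of two independent Binomial(40, 0.5)/40 proportions has SD √(2·0.25/40) = 0.112.
- P(difference ≥ 15 points) = 0.218
- P(difference ≥ 20 points) = 0.093

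Fixing the total number of each operation among 80 patients (hypergeometric) gives 0.263 and 0.117 at a 50:50 split, and 0.222 and 0.087 at 30:70. The answer is of the same order either way.

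**Step 2: what a 15-point imbalance does.** Shift = 0.15·D. The within-operation standard error of the arm difference is 20·√(2/40) = 4.47 mm.

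**Step 3: what pooling costs on average.** Variance added by mixing operations = 0.5·0.5·D² = D²/4. Share of total variance = (D²/4)/(400 + D²/4). For power, take the effect detectable with 80% power at SD 20, which is 2.8016·4.47 = 12.5 mm, and recompute with the enlarged SD √(400 + D²/4). This uses the two-means formula as an approximation to the rank test.

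| D (mm) | Shift at 15-point imbalance (mm) | Shift ÷ 4.47 | Share of VAS variance | Pooled SD (mm) | Power when pooled |
|---|---|---|---|---|---|
| 5 | 0.75 | 0.17 | 1.5% | 20.2 | 79.4% |
| 10 | 1.50 | 0.34 | 5.9% | 20.6 | 77.6% |
| 15 | 2.25 | 0.50 | 12.3% | 21.4 | 74.6% |

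Widening the assumptions to D = 5 to 20 mm, SD 20 to 25 mm and a 30% or 50% share of total mastectomy gives pooled power of 71 to 80%.

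**Step 4: the two costs are one cost.** At D = 15 mm the chance shift has SD 0.1118·15 = 1.68 mm. Combined with the within-operation error, √(4.47² + 1.68²) = 4.78 mm, which is the pooled standard error 21.36·√(2/40) = 4.78 mm. The pooled standard error already contains the chance imbalance, so the shift in step 2 and the power loss in step 3 must not be added together.

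No figure can be put on the hospital effect from the documents.

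**The case against.** The strongest objection is about validity. Under random allocation an unstratified Mann-Whitney test keeps its type I error, and step 4 shows that imbalance in operation type is part of the sampling error it allows for. That stands. A reader might infer that the pooled test gives a biased estimate of the drug's effect on pain; the documents do not support this. The proviso is that allocation is in fact random. The rule that forces allocation after a bias is seen raises its own question there, separate from this point.

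Other objections, and what remains of them:
- **The size is assumed and small.** True. If the operations differ little in pain at 24 hours, the gain is close to nil. The case rests on the low cost of the change.
- **Other predictors exist.** True. HADS and STAI are recorded before treatment, and section 3 links anxiety with postoperative pain. One cannot say that operation and hospital are the main prognostic information available.
- **The axillary-dissection rule.** A reader might infer from section 5 (3) ③ that the protocol itself regards extent of surgery as decisive for outcome. It gives no reason for that rule, so this is conjecture and no contradiction can be built on it.
- **The statistical analysis plan may adjust.** It might; it was not available. But allocation factors have to be settled before patients are allocated, and the protocol does name its tests.
- **The list of factors is open-ended.** Operation or hospital could be added under it, but an open list commits the trial to neither.

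**Conclusion.** The point holds as a minor one. The protocol mixes two operations and two hospitals, names neither for balancing, and states an unstratified test for VAS. The consequence is some loss of precision and exposure to chance imbalance on two secondary endpoints. It is not systematic bias, and no effect on the salivary amylase endpoint is claimed.

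Under the stated assumptions (50:50 split, SD 20 mm, operation effect 5 to 15 mm), a comparison with 80% power when stratified falls to about 75 to 79% when pooled. An imbalance of at least 15 points arises roughly once in four or five trials, and a 15-point imbalance moves the VAS difference by at most about half a standard error. None of these three inputs is in the documents, and the hospital contribution is unquantified.

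**What to change.** - **Section 4 ④ [2]:** add planned operation (total or partial) and hospital as named stratification or minimisation factors, applied from the first patient and not only after an imbalance is noticed. Age may be kept; nothing here shows that the existing factors should be dropped.
- **Section 4 ④ [1]:** add both variables to the items recorded at baseline.
- **Section 4 ⑦:** for VAS, replace the pooled Mann-Whitney test by the van Elteren (stratified Wilcoxon) test over operation and hospital. For QOR, whose test the protocol does not name individually, use the same test or a linear model with both terms.
- **If allocation has begun:** leave it as it is and change only the analysis, preferably before outcomes are compared by arm.

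The cost is protocol wording and two recorded items that are known for every patient. No extra patients or measurements are needed. The downside is up to four small strata, or two degrees of freedom in a model.

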**11. [Viewing original materials]**

At the conducting medical institution, the principal investigator ensures that all records, including source materials, can be viewed during monitoring, auditing and investigations by accredited clinical research review committees and regulators.

**12. [Method of storing and disposing of samples / information (including materials related to information used in research)]**

The information obtained from this study will be kept strictly until 10 years have passed after all research plans have been completed. Regarding the information obtained at all facilities, all or part of the information that can identify an individual is removed from the personal information and anonymized by numbering. The obtained patient information and questionnaire results will be stored in a locked drawer of the Niigata University Anesthesiology Laboratory in an anesthesiology state and will not be taken out. The correspondence table and patient information will be stored separately, and care will be taken to ensure that information is exchanged between hospitals appropriately. The person in charge of storage shall be [name], the person in charge of research. When discarding the obtained information, shredder the information left on the paper medium and erase the information left in the file format using data erasure software. The results of this research will be published by presenting them at academic meetings such as academic societies and academic journals, but in that case as well, consideration will be given to not being able to identify individuals, and the results of statistical analysis will be the main focus.

If the research is rejected or the research is discontinued after consenting to the research, all the information on the patients to be studied collected up to that point will be discarded and no further data will be collected.

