**Procedures for handling missing, rejected and abnormal data**

If there is missing data on the primary endpoint, the patient's data will be excluded from the analysis. If it is found that missing data exists in the secondary evaluation item during data analysis, the item is treated as a deletion value and data analysis is performed.

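### Criterion ④ in section 5 (3), with the discard sentence in section 12, permits discretionary removal of randomised patients and loss of their data in an open-label trial

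*Protocol*

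**What the plan says.** Section 5 (3) of the protocol has four cancellation criteria. ① is the patient declining or withdrawing consent. ② is "When the entire research is canceled". ③ is axillary dissection after a positive sentinel node. ④ is open-ended: "When the person in charge of research determines that it is appropriate to discontinue the research for other reasons". It names no grounds, no time limit, and no blinded or independent decision.

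Section 4 ④ describes the design as "Multicenter / Open Label / Superiority test by forced random sampling". The control group takes no study drug.

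Section 12, on storage and disposal, sets the data consequence. Its trigger is "If the research is rejected or the research is discontinued after consenting to the research", and in that case "all the information on the patients to be studied collected up to that point will be discarded and no further data will be collected".

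Two further rules bear on who is analysed. Under the missing-data heading after section 12: "If there is missing data on the primary endpoint, the patient's data will be excluded from the analysis". In section 5 (4): "Patients who refuse to take the second dose after the first dose and withdraw from the study are also excluded from this study". The protocol nowhere says that all randomised patients are analysed as allocated.

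**The concern.** Most protocols let an investigator stop a patient's participation for unlisted reasons, and that does no harm when the patient stays in the analysis. Here the same decision appears to remove her data as well. The decision may be made by someone who knows the arm and has some idea of how the patient is doing. Patients removed this way need not be a random subset of those randomised, so the protection that randomisation gives to the comparison can be lost.

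The primary endpoint ("Primary endpoint: Salivary amylase level") and the self-rated secondary endpoints (HADS, STAI, QOR, pain VAS) are exposed in the same way. A later statistical analysis plan could define an analysis set, but it could not restore values that the protocol had ordered discarded. The point therefore concerns a stated rule and not an omission.

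The route differs from refusal of the second dose, which only the yokukansan arm can do, and from axillary dissection, which is triggered by a biopsy result. Criterion ④ is discretionary and can be applied in either arm.

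**Working it through.** **Step 1. Does ④ concern a single patient?** Its wording speaks of discontinuing the research, which could mean the whole trial. But ② already covers that, and ① and ③ are events in one patient. If ④ also meant the whole trial it would largely repeat ②. The per-patient reading is the natural one.

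**Step 2. Does the discard sentence reach ④?** The trigger in section 12 names two events after consent: rejection and discontinuation. Rejection covers the patient's own refusal, so discontinuation adds something beyond it, and an investigator's decision fits. This is an inference, because the sentence does not name ④.

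**Step 3. When could it bite?** The realistic window runs from allocation to the assessment 24 hours after surgery. Within it, the salivary amylase reading taken just before surgery may already exist.

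**Step 4. The plan's own figure.** No figure is disputed; the group size is only an input to the next step. Section 4 ⑤ gives about 40 per group, 80% power, significance level 0.05, a 75% success rate and a difference of 0.3. Reading 0.3 as 30 percentage points, so 45% in controls (an assumption), the two-sided pooled formula gives

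n = [1.960 × √(2 × 0.60 × 0.40) + 0.842 × √(0.75 × 0.25 + 0.45 × 0.55)]² / 0.30²
= [1.358 + 0.555]² / 0.09 ≈ 40.7, so 41 per group. The plan's figure of about 40 is reproduced.

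**Step 5. Illustration of size.** Inputs: 40 per arm (section 4 ⑤) and P<0.05 with a t-test (section 4 ⑦). Assumptions: standard normal outcome with higher values worse, no true effect, two-sided test, k patients removed from the intervention arm only, 40,000 replicates. The protocol gives no expected number of cancellations, so k and the way patients are selected are also assumptions. A false positive in favour of yokukansan means P<0.05 with the difference in its favour.

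| Removal | k | Shift (SD) | False positive favouring yokukansan | Two-sided error |
|---|---|---|---|---|
| None | 0 | 0.00 | 2.5% | 5.0% |
| Random from worse half | 1 | 0.02 | 3.0% | 4.9% |
| Random from worse half | 2 | 0.04 | 3.65% | 5.1% |
| Random from worse half | 4 | 0.09 | 5.3% | 6.2% |
| Exactly the worst | 1 | 0.06 | 4.6% | 6.1% |
| Exactly the worst | 2 | 0.10 | 7.5% | 8.4% |
| Exactly the worst | 3 | 0.15 | 10.9% | 11.5% |
| Exactly the worst | 4 | 0.19 | 14.9% | 15.2% |

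Simulation error is about 0.1 percentage points near 5% (√(0.053 × 0.947 / 40,000) ≈ 0.0011). Repeat runs gave 5.3% to 5.5% for four removals from the worse half.

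Hand check of the milder rows: the worse half of a standard normal has mean √(2/π) ≈ 0.80, so the shift is about k × 0.80 / (40 − k). For k = 1, 2 and 4 this gives 0.80/39 = 0.02, 1.60/38 = 0.04 and 3.20/36 = 0.09, in agreement with the table.

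With the Mann-Whitney test, which the plan names for non-normal variables, removing exactly the 1 to 4 worst gives a two-sided error of 5.6% to 12.65%.

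**The case against.** The strongest reply is that the discard sentence was never meant for ④. It is awkwardly worded, sits in a section on handling personal information, and can be read as covering only patients who refuse or revoke participation. On that reading nothing in section 5 (3) removes a ④ patient's data, and she would be excluded only if her amylase value were missing. The link is indeed not explicit. But the sentence names discontinuation separately from rejection, so a site following the plan as written could well discard the data. If the scope is in doubt, it needs settling in the text.

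A second reply is that the fault lies in section 12 and affects other cancellation routes too. That is fair, and the fix below includes that sentence. Criterion ④ deserves its own mention because it is the route with no stated grounds.

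Third, the analyst is separate from the principal investigator (section 4 ⑦). This helps little, because removal would happen before the data reach the analyst.

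A reader might infer three stronger things that the documents do not support:

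- *That completed patients can be deleted once their 24-hour ratings are known.* After the last scheduled assessment no study participation is left to discontinue, so this strains the wording.
- *That nothing remains for anyone to check.* Section 11 opens all records, including source materials, to monitoring and audit, and section 27 provides for both. These do not guarantee that discarded study values survive, and a cancellation under ④ followed by disposal would comply with the plan. But some trace would be expected.
- *That the false-positive rate will reach 10% or more.* Those rows need someone to pick exactly the worst outcomes. Under milder selection, one or two removals leave the two-sided error essentially nominal (4.9% and 5.1%).

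**Conclusion.** The concern stands in a limited form. The discretionary clause is ordinary. Combined with the discard sentence in section 12, in an open-label trial, it permits exclusion after randomisation that can be related to arm and prognosis, and the lost values could not be used in a sensitivity analysis. The documents support the statement that this can bias the comparison; they do not show that it will, or that the stated significance level fails.

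Size and direction are unknown. As an illustration, 1 to 4 removals from the worse half of the intervention arm shift the difference by 0.02 to 0.09 SD and raise the false-positive rate in favour of yokukansan from 2.5% to about 3.0% to 5.3%. The upper bound, with exactly the worst removed, is 4.6% to 14.9%. The conclusion rests on two readings that are natural but not explicit: that ④ is per patient, and that the discard sentence reaches it. It alleges no misconduct, since unintended selection is enough.

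**What to change.** Leave the grounds for stopping in section 5 (3) unchanged and change only the data consequence.

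1. In section 5 (3), state that after allocation a decision under ④ ends further study participation only. Data already collected (amylase, HADS, STAI, QOR, pain VAS, analgesic use) are kept, and the patient is analysed in her allocated group. Later scheduled values are collected where she still consents.
2. In section 12, limit the discard sentence to patients who themselves withdraw consent to the use of their data.
3. Record the date, reason and arm of each ④ decision, and report the counts by arm.

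The cost is about one sentence in each of the two sections and a short log. No extra patients or procedures are needed. The downside is that a few atypical patients stay in the analysis and add a little variance.
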